#### Patient Health Questionnaire-9

The Patient Health Questionnaire-9 (PHQ-9) [24] is a validated 9-item self-report measure assessing symptoms of depression. Responders indicate the frequency of symptoms on a scale of 0=not at all to 3=nearly every day. Scores can range from 0 to 27, with an additional qualitative question regarding the level of difficulty caused by symptoms ranging from no difficulty at all to extreme difficulty. Scoring interpretation is as follows: 1-4 (minimal depression), 5-9 (mild depression), 10-14 (moderate depression), 15-19 (moderately severe depression), and 20 and greater (severe depression). Kroenke et al [24] found that a PHQ-9 score ≥10 exhibited a satisfactory sensitivity of 88% and a specificity of 88% for major depressive disorder.

#### Perinatal-Post Traumatic Stress Disorder Questionnaire-II

The Perinatal-Post Traumatic Stress Disorder Questionnaire-II (PPQ-II) [25] is a validated 14-item self-report measure assessing symptoms of trauma among postpartum individuals. Frequency and duration of symptoms are rated on a 5-point Likert scale from 0=not at all to 4=often for more than a month, with total scores ranging from 0 to 56. Scores of 19 above indicate a clinical range of symptoms that would benefit from additional support. Komurcu Akik and Durak Batigun [25] found that the PPQ-II demonstrates validity and reliability as a scale for assessing the perinatal post-traumatic stress symptoms experienced by mothers.

### The M-PSP Intervention

The Perinatal Skills Program was developed within Maya*,* a CBT skills app that is customizable and allows for the creation of individualized programs for multiple populations. M-PSP was adapted from one such program, Maya-Cognitive Behavioral Skills Program (M-CBT), which was a 12-session program that provided gold-standard, evidence-based strategies to help young adult users learn tools to manage anxiety and low mood. Preliminary data from a feasibility and acceptability trial of M-CBT suggest that the app is feasible and acceptable, and results showed a substantial decrease in both depression and anxiety from pre- to post-intervention [26]. In response to rising maternal mental health needs, an expert team of clinical psychologists specializing in CBT and reproductive psychiatrists with expertise in perinatal mental health adapted M-CBT into M-PSP. The team also consulted with physicians within pediatric primary care and obstetrics departments to better understand the needs of expectant and new parents. Changes to the original program included tailoring language and examples to address concerns that are common during and after pregnancy, as well as modifying skills as appropriate for the perinatal population. Several new skills were added, such as tools for managing communication and relationships as an expectant or new parent (Multimedia Appendix 1).

Users can work through each M-PSP session on their own schedule and are able to unlock up to 2 sessions per week. This pacing mirrors typical CBT session structure, allowing time for homework and practice between sessions, which is crucial for skill development and mastery [27,28], and acknowledges research showing that most people engage with apps for a limited duration, necessitating a structured yet flexible format to maximize engagement and effectiveness [29,30]. Each session in the program includes 3 main sections: learn (where new information and skills are shared), practice (where users can try out the skills they learned), and review (wrap-up of key lessons and takeaways). Users are introduced to a range of evidence-based tools throughout the 12 sessions (Table 1). There are also homework assignments for each session allowing users to practice what they have learned throughout the week. Users can individualize their experience by entering and tracking mood and anxiety ratings, planning for real-world skills use, personalizing examples, choosing preferred exercises to try, and reflecting on skill practice. The app has been programmed to help users see their progress through the app and track change toward self-identified goals. Users are also able to make use of tabs within the app for quick access to specific information, such as videos, skill practice, and favorite tools. Study staff have weekly meetings to ensure protocol is adhered to.

**Table 1 table1:** M-PSP^a^ session content.

Session	Session objectives and content
Session 1: Understanding symptoms and treatment	Psychoeducation on perinatal anxiety and mood symptoms Sleep tips for pregnancy and post partum. Identifying common perinatal patterns of thoughts, feelings, and behaviors
Session 2: Facing challenges	Identifying how emotions impact behavior during the perinatal period Learning to gradually approach and overcome challenging tasks “Face It!” exercise to craft an individualized goal ladder for daily practice
Session 3: Shifting thoughts	Cognitive restructuring techniques to reframe unhelpful thinking Guidance on effective communication and managing evolving relationships Introduction of “TINTED Thoughts” exercises to recognize and correct cognitive distortions
Session 4: Relaxing your body and mind	Introduction to relaxation exercises and audio-guided muscle relaxation meditation session. Distress tolerance tips to manage stressful moments “Face It!” exercise to craft an individualized goal ladder for daily practice
Sessions 5-10: Practice and use skills	Revisiting the list of challenging situations and tracking progress Continued practice of helpful thoughts and “Face It!” exercises Introduction to problem-solving skills and additional distress tolerance exercises
Sessions 11-12: Maintenance and relapse prevention	Guided selection of an exercise for ongoing skill practice Skill review and reflection exercise Guidance on next steps to support sustained mental health

^a^M-PSP: Maya-Perinatal Skills Program.

### Procedure

As of October 2024, the study is open to recruitment. Recruitment strategies involve advertisements through listservs, clinician information sessions, and flyers within inpatient and outpatient departments. Interested individuals can complete a digital contact information form via a Health Insurance Portability and Accountability Act–compliant survey platform or have their providers complete the contact forms on their behalf.

Study staff reach out to individuals who have completed the form to screen for eligibility. Eligible participants are given further details about study involvement and complete informed consent. Study staff help participants download the app and provide an orientation, with recommendations to use the program for 10 minutes a day, 4 days a week. While it is recommended to complete the program within 6 weeks, sessions can be completed at the participant’s convenience. All participants will be allowed up to 18 weeks for completion in order to account for delays or interruptions that may have occurred during pregnancy or after labor and delivery. Within 1 week of the study orientation, the research assistant will conduct a brief 5-minute phone check-in using a scripted protocol to ensure participants have been able to access and start the app, check on potential technical issues, and answer any questions related to app navigation.

Throughout participation, participants will be able to complete up to 2 sessions per week and will complete the in-app feedback surveys after each session. They will also be sent a text to their phone with a link to complete the daily PST. Additional assessments occur at midpoint (following completion of session 6), post (completion of session 12), and follow-up (6 weeks after post). These assessments include the staff-led feedback interviews via phone or videoconference, as well as the uMARS and all symptom measures. When risk items are endorsed on the daily PST, symptom measures, or during the assessments, study staff are notified and the participant is contacted by a licensed provider to conduct a formal risk assessment and safety plan as necessary.

To aid in retention and study completion, study staff monitor app completion progress and maintain contact with participants to schedule feedback interviews (Table 2). Through these methods, staff are able to problem-solve technical difficulties and other barriers to session completion as needed. Participants are encouraged to reach out via email or phone with any questions or concerns. Study staff follow institutional review board (IRB) guidelines to report any adverse events within the required timeline.

**Table 2 table2:** SPIRIT^a^ checklist.

	Prestudy	Intake	Weeks 1-6	Midpoint	Weeks 7-12	Post	6-week follow-up
Contact form	✓						
Eligibility screen		✓					
Informed consent		✓					
Download of Maya		✓					
Background questionnaire		✓					
App sessions			✓		✓		
In-app feedback			✓		✓		
Symptom measures		✓		✓		✓	✓
Daily symptom tracker			✓	✓	✓	✓	✓
Feedback interview and uMARS^b^				✓		✓	✓
Adverse event monitoring	✓	✓	✓	✓	✓	✓	✓

^a^SPIRIT: Standard Protocol Items: Recommendations for Interventional Trials.

^b^uMARS: user version of the Mobile Application Rating Scale.

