### Participants

The study is currently open to recruitment, with the aim to recruit 50 pregnant or postpartum individuals across all sites. In prior studies, feasibility studies often include a sample size of approximately 50 participants, which is deemed appropriate to ensure robust findings and comprehensive insights into app usability and effectiveness, balancing the need for inclusivity and accurate representation while accounting for potential participant attrition in digital mediums [14,15]. The inclusion criteria for study participation include (1) aged 18 years or older; (2) pregnant or up to 12 months post partum; (3) scoring 8-16 on the Edinburgh Postnatal Depression Scale (EPDS) [16] or 5-14 on the Generalized Anxiety Disorder-7 Scale (GAD-7) [17]; (4) able to read and speak English; (5) have access to a smartphone or mobile device capable of receiving SMS pushes and supporting Qualtrics Surveys and App (Weill Cornell Medicine); and (6) available to speak by phone or secure videoconference. The exclusion criteria include (2) safety concerns at the time of enrollment; (2) current substance use disorder; (3) current symptoms of psychosis or mania; and (4) history of bipolar or psychotic disorder.

M-PSP is designed to address mild-to-moderate anxiety and depression symptoms and may not be appropriate for more severely impaired individuals. In order to secure feedback from participants matching the app’s target population, the inclusion criteria include those scoring in the mild-to-moderate range on anxiety and depression ratings. Participants with safety concerns at the time of intake, including recent suicidal ideation or self-harm, are excluded as they are at higher risk for heightened symptoms and risk in the perinatal period. Eligibility is not impacted by receipt of clinical care outside of the study, and participants are not excluded if they are receiving concurrent treatment for depression or anxiety.

Study participants may be disenrolled from the study if they are nonresponsive to 16 outreach attempts across 4 consecutive weeks or if their pregnancy ends.

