##### Passive Data Collection

M-PSP passively collects data, encompassing information captured without active user input, such as when sessions were completed, frequency of program usage, and program completion. These data points will serve as measures of program feasibility and user engagement.

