Despite these limitations, this study is an important step in helping to fill the gap between an increasing maternal mental health crisis and barriers to appropriate support. By using a community-based-participatory research model, the development team has been able to consider input from researchers and clinicians across different specialties and will be able to incorporate feedback from end users through each stage of program development. Once feedback has been considered and incorporated into the program, the team will look to conduct future studies to assess the effectiveness of the tool in helping perinatal individuals manage anxiety and mood symptoms. Per guidelines on progressing from a pilot trial to a fully powered randomized controlled trial (RCT) [33], the research team has outlined a number of criteria that will influence the next steps. To ensure adequate participant numbers for an RCT, the pilot trial will need to demonstrate a 50% retention rate between screening and enrollment. The team will also move forward if 75% of participants complete primary outcome measures, which consist of feasibility, acceptability, and usability feedback interviews and surveys. While the study team will track adherence to the intervention (ie, completing M-PSP sessions), this will not be used as a criterion for progressing to a full RCT as nonadherence may be attributable to feasibility or acceptability concerns that the pilot study intends to illuminate so that future versions of the app can be modified prior to an RCT.

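### Interviews, uMARS and later symptom scales fall due only on finishing session 6 or 12, so early stoppers give little feedback and adherence re-enters a progression rule meant to exclude it

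*Protocol article*

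**What the plan says.** **Timing.** The Procedure section of the protocol article states: "Additional assessments occur at midpoint (following completion of session 6), post (completion of session 12), and follow-up (6 weeks after post". On content it adds: "These assessments include the staff-led feedback interviews via phone or videoconference, as well as the uMARS and all symptom measures". The in-app surveys follow the same logic, since participants "will complete the in-app feedback surveys after each session".

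**Pace.** Participants may do up to two sessions a week. The Procedure section says: "While it is recommended to complete the program within 6 weeks, sessions can be completed at the participant’s convenience". The outer limit is 18 weeks. No assessment is tied to that limit, to stopping or to disenrolment.

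**What does not depend on sessions 6 and 12.** Passive app data, listed as a primary outcome, cover items "such as when sessions were completed, frequency of program usage, and program completion". The daily tracker is texted throughout participation, and symptom scales are also taken at intake.

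**Progression.** The Discussion states: "The team will also move forward if 75% of participants complete primary outcome measures". It defines those measures as the feedback interviews and surveys. It says of session adherence that "this will not be used as a criterion for progressing to a full RCT", because nonadherence may reflect the feasibility or acceptability problems that the pilot is there to bring to light.

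**The concern.** The two sections pull against each other. The Discussion wants to learn why people do not keep up with the sessions, and for that reason leaves adherence out of the go decision. The Procedure section makes the richest sources on that question available only from people who have kept up, at least to session 6.

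Three things are at stake:

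- **The go rule.** If every measure that counts toward the 75% is triggered by sessions, low adherence can fail the rule even when people are willing to give feedback.
- **The acceptability and usability estimates.** The uMARS and interview findings describe those who continued, who probably liked the app better than those who stopped.
- **The secondary aim.** The Data Analysis Plan intends to correlate symptom and acceptability scores with app completion. Among people with a post assessment, completion takes a single value.

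**Working it through.** **Inputs from the protocol article**

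- Target sample, Participants section: "with the aim to recruit 50 pregnant or postpartum individuals across all sites".
- Threshold: 75% of participants (Discussion).
- Triggers: session 6, session 12, and 6 weeks after post (Procedure).
- The article gives no expected adherence, response rate or uMARS spread. The values used below are assumptions, shown as ranges. No power or sample-size figure rests on this point, so there is none to reproduce.

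**Step 1. Who is asked what, as written**

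| Participant | Interview and uMARS due | Symptom scales due after intake |
|---|---|---|
| Stops before finishing session 6 | none | none (daily tracker only) |
| Finishes session 6, stops before finishing session 12 | midpoint only | midpoint only |
| Finishes session 12 | midpoint, post, follow-up | midpoint, post, follow-up |

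In-app surveys are due for each session finished, and usage data come from all users. Someone in the second row is interviewed before stopping, so no scheduled interview covers why they stopped.

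**Step 2. The ceiling on the 75% rule**

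0.75 × 50 = 37.5, so 38 participants are needed. The share completing the measures equals the share reaching the triggering session multiplied by the response rate among them.

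- With 100% response, at least 75% must reach that session. If it is session 12, average continuation per session must be 0.75^(1/12) = 0.976. If it is session 6, it must be 0.75^(1/6) = 0.953.
- With 95%, 90% or 80% response, the share reaching the session must be 0.75/0.95 = 78.9%, 0.75/0.90 = 83.3% or 0.75/0.80 = 93.8%.

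The exact binomial probability of at least 38 successes in 50, with success probability equal to reach × response, is:

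| Share reaching the triggering session | 100% response | 90% response |
|---|---|---|
| 60% | 0.013 | 0.001 |
| 70% | 0.22 | 0.04 |
| 75% | 0.51 | 0.13 |
| 80% | 0.81 | 0.33 |
| 90% | 0.999 | 0.86 |

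If the assessments were due whatever the number of sessions done, 90% response would give a probability of 0.999 at any adherence.

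**Step 3. Selection in the uMARS**

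Suppose satisfaction and persistence are jointly normal with correlation r, and a share c reaches the assessment. The mean among those assessed is then too high by r × φ(z)/c SD, where φ is the standard normal density and z cuts off the upper share c.

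- c = 0.7: 0.10 to 0.20 SD for r = 0.2 to 0.4
- c = 0.5: 0.16 to 0.32 SD
- c = 0.3: 0.23 to 0.46 SD

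The multiplier φ(z)/c falls as c rises. More people reach session 6 than session 12, so for the same r the midpoint uMARS is less affected. On the rating scale, if those not assessed would have scored 0.5 to 1.0 point lower, the mean is too high by (1 − c) × gap. That is 0.25 to 0.50 points at c = 0.5 and 0.125 to 0.25 at c = 0.75.

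**Step 4. The planned correlations**

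Everyone with an observed post score has finished 12 of 12 sessions. The variance of program completion in that group is zero, so its correlation with post scores is undefined. At midpoint, completion is cut off below at 6 of 12. Intake scores can still be correlated with completion, and frequency or duration of use can still be correlated with post scores.

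**The case against.** The best case on the other side has several parts, and much of it stands.

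- A reader might infer that people who stop early are never asked anything, or that all primary outcomes come from those who persist. Neither is right. Someone who stops after session 5 has been due five in-app surveys, and the In-App Surveys section links some of those items to feasibility and acceptability. Usage data, also primary, need neither session 6 nor session 12. Someone who stops at session 9 has been due the midpoint interview and uMARS.
- A reader might infer that the go rule fails whenever fewer than 38 people finish session 12. The Discussion does not say that post must be completed. If midpoint suffices, the gate is session 6.
- A reader might fear a false go from inflated ratings. No progression criterion uses a uMARS score. With enrolled participants as the denominator, the session triggers make a go harder, not easier.
- A reader might see a clash between Table 2 and the text. Two sessions a week is a maximum. At one a week, session 6 falls at week 6 and session 12 at week 12, which fits Table 2. The week labels could be clearer, but this is not a material contradiction.
- The article condenses a fuller protocol that may contain an exit assessment. It also describes a check-in call within a week, continuing staff contact and up to 16 outreach attempts before disenrolment.

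This contact is not described as an interview or uMARS for those who stop. The printed triggers and the printed progression rule still conflict. The Data Analysis Plan does not mend this: simple imputation cannot supply an interview that was not held, and imputing scores from those who continued carries their selection forward.

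**Conclusion.** The concern holds in a limited form. The feedback interviews, the uMARS and the post-intake symptom scales other than the daily tracker depend on finishing session 6 or 12. The progression rule that sets adherence aside counts interviews and surveys that are all triggered by sessions.

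The ceiling in Step 2 follows from the text and needs no assumption beyond reading the 75% as a share of enrolled participants: no more can meet the rule than finish session 6, or session 12 if post is required. The probabilities depend on assumed adherence and response.

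The upward bias in uMARS and interview feedback is likely in direction but uncertain in size. The 0.10 to 0.46 SD applies to session 12, under assumed completion of 30-70% and correlation of 0.2-0.4. The undefined correlation between program completion and post scores is a direct consequence of the trigger.

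This should be fixed, but it does not undermine the whole pilot: usage data, in-app surveys and the tracker still give information on people who stop early, and the article itself calls the findings preliminary.

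**What to change.** Keep the session triggers and add a fallback:

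- **Midpoint set:** at session 6 or at a fixed week chosen in advance, whichever comes first.
- **Post set:** at session 12, at week 18, or at stopping or disenrolment, whichever comes first. For those who stopped, the interview should ask why.
- **Follow-up:** 6 weeks after the post set, for everyone.
- **Progression rule:** state which timepoint or timepoints count toward the 75%, and use all enrolled participants as the denominator.
- **Reporting:** show uMARS, interview themes and symptom scores separately for those who stopped early.
- **Table 2:** add a note on how the week labels relate to the 6-week recommendation and the 18-week limit.

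The cost is a minor ethics amendment and a few extra calls by existing staff. Some who have stopped will decline or, if disenrolled for nonresponse, will not be reachable. Ratings may look less favourable. With 32 of 50 enrolled in October 2024, the change could serve the remaining 18 and those still within their 18 weeks, but may come too late for some already enrolled.

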### Data Analysis Plan

To analyze qualitative data from the feedback interviews, the grounded theory approach [31] will be used to review all responses and develop a consensus on existing themes. The data will then be systematically coded using these themes in order to identify core concepts and response patterns to derive meaningful interpretations of the feedback.

Data passively collected from the app will be transformed into practical means and ranges that will be used to understand user engagement and program feasibility. Means and SDs will be computed for demographic information and relevant symptom and acceptability questionnaires. Continuous scores from symptom scales and acceptability questionnaires will be analyzed in relation to app use and engagement. Correlations between these variables with be assessed using either Pearson or Spearman correlation depending on data distribution. For example, we will examine the correlation between EPDS symptom scores and app completion rates to explore whether postpartum depression symptoms are related to program feasibility. Hypothesis testing will be conducted with a *P* value=.05 as the threshold for statistical significance, and clinical significance will be considered for correlations that meet a meaningful cutoff (eg, 0.6 or 0.8). This analysis will help identify any demographic characteristics or symptoms that may require greater attention in future iterations of the program to ensure its effectiveness for a broad range of perinatal individuals. For participants who dropped out before study completion, all available data will be included, and any missing data will be handled using simple imputation. A correlation matrix will be generated to explore the relationships between symptom scales (eg, EPDS and GAD-7) and app engagement variables (eg, frequency of use, duration of use), allowing us to investigate possible associations without the need to correct for multiple testing in this exploratory pilot study.

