## Methods

### Aims

The primary aim of this study is to assess the feasibility and acceptability of M-PSP. Specifically, the team will evaluate the mobile app–based program in terms of user satisfaction, perceived use of the program, and engagement with the program. A secondary aim of the study is to look for any associations between program completion and engagement with mental health symptoms.

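### Symptom scores are to be correlated with app use unadjusted and at no named visit; for scores taken after intake, this mixes who engages with whether engagement goes with symptom change

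*Protocol article*

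**What the plan says.** The secondary aim (Aims) is to "look for any associations between program completion and engagement with mental health symptoms". For this the Data Analysis Plan says: "Continuous scores from symptom scales and acceptability questionnaires will be analyzed in relation to app use and engagement". The method follows: "Correlations between these variables with be assessed using either Pearson or Spearman correlation depending on data distribution". One example is given: "we will examine the correlation between EPDS symptom scores and app completion rates to explore whether postpartum depression symptoms are related to program feasibility". On testing, the section says: "Hypothesis testing will be conducted with a *P* value=.05 as the threshold for statistical significance". It also offers 0.6 or 0.8 as example cutoffs for a clinically meaningful correlation. A matrix of symptom scales against engagement variables is to be produced "without the need to correct for multiple testing in this exploratory pilot study".

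The section does not say which visit supplies the symptom score. It names no covariate, partial correlation or change score.

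Four other places bear on the point:
- Table 2 places the symptom measures at intake, midpoint, post and the 6-week follow-up. The daily tracker has its own row, with no tick at intake.
- Procedure ties midpoint to finishing session 6 and post to finishing session 12. Follow-up comes 6 weeks after post.
- Participants states that "participants are not excluded if they are receiving concurrent treatment for depression or anxiety". The same section admits both pregnant and postpartum people.
- Design states that there is no comparison arm.

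**The concern.** A symptom score after intake carries two things: how unwell the person was at the start, and what has happened since. If people with more symptoms at intake use the app less (or more), the later score will correlate with use even when use has nothing to do with change. If the intake-to-use correlation is positive, the induced correlation is positive too and can hide a real tendency for heavier users to improve. Outside treatment can act in the same way, and no control group is available to show it.

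At stake is how the secondary aim is read. The section intends to use these correlations to decide which symptoms or characteristics need attention in later versions of the program. A correlation at post that reflects intake severity could be taken as information about response to the program. The intake score that would separate the two is already scheduled.

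**Working it through.** The plan gives no figure to reproduce: the sample of 50 rests on precedent, and the Discussion says the study is not powered for significance.

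**Inputs from the documents.** n = 50 (Participants); threshold .05, taken as two-sided (Data Analysis Plan). A smaller n of 38 (0.75 × 50 = 37.5, rounded up) borrows the 75% progression criterion in the Discussion, purely as a scenario.

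**Assumed inputs.** The correlation of intake with post score, ρ, is 0.5 to 0.7. The correlation of intake score with use is -0.3, with a wider range of 0.2 to 0.5 in absolute value.

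**Step 1: induced correlation.** If use and post score are related only through the intake score, r(post, use) = ρ × r(intake, use). So 0.5 × -0.3 = -0.15, 0.6 × -0.3 = -0.18 and 0.7 × -0.3 = -0.21.

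**Step 2: critical value.** |r| = t/√(df + t²) with df = n - 2. This gives 0.279 at n=50 and 0.320 at n=38.

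**Step 3: chance of P<.05 with no link between use and change.** By Fisher's z, take z = atanh(r) × √(n - 3) and compare with ±1.96. For |r| = 0.15 and n=50: 0.1511 × √47 = 1.036, so the chance is 1 - Φ(0.924) + Φ(-2.996) ≈ 0.179.

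**Step 4: residual SD after adjusting for intake.** The factor is √(1 - ρ²).

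| ρ | induced r | P<.05, n=50 | P<.05, n=38 | residual SD factor |
|---|---|---|---|---|
| 0.5 | -0.15 | 17.9% | 14.5% | 0.866 |
| 0.6 | -0.18 | 23.9% | 19.0% | 0.800 |
| 0.7 | -0.21 | 30.9% | 24.3% | 0.714 |

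Over the wider range the induced |r| runs from 0.5 × 0.2 = 0.10 to 0.7 × 0.5 = 0.35. The chance of P<.05 then runs from about 11% to 71% at n=50 and from 9% to 58% at n=38.

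**Step 5: simulation check** (40,000 trials per setting, multivariate normal, no link between use and change, n=50).
- With ρ = 0.5 and |r(intake, use)| = 0.3, the raw correlation rejects in 18.4% of trials and the partial correlation given intake in 5.0%.
- With 0.6 and 0.3, the figures are 24.2% and 4.9%.
- Over all five settings run at n=50, the partial correlation rejects in 4.9% to 5.3%.
- A change score is not a substitute: it rejects in 18.0% and 15.2% of trials in the two settings above.

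**Step 6: the 0.6 cutoff.** A raw |r| of 0.6 or more occurs in at most 1.4% of simulated trials at n=50 and 2.8% at n=38, both in the most extreme setting (0.7 and 0.5).

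**Step 7: spread in completion.** Since post is reached by finishing session 12, observed post and follow-up scores come from people who completed all 12 sessions. Their completion rate hardly varies, so its correlation with those scores has little to work on unless it leans on imputed values. Adjusting for the intake score does not restore that spread.

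**The case against.** The strongest reply is that the plan never commits to the analysis criticised. No visit is named, and the one worked example asks whether symptoms relate to feasibility, which the unadjusted intake score answers properly. The aim is association, the Discussion states no hypotheses for it, and findings are to be treated as preliminary. A condensed article may also leave visit and covariates to a fuller document.

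Much of this stands. A reader might infer that the plan leaves the intake score out, or that post-program scores are the ones to be correlated; the text says neither. The concern is therefore conditional on the use of a score taken after intake. But the article does state a method, an unadjusted correlation, and applies it to symptom scales without limiting it to intake. Three of the four scheduled assessments fall after use has begun. Exploratory status excuses low power and uncorrected testing, but it does not separate the two meanings of a post-intake correlation.

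The limits on adjustment also stand:
- A reader might assume that every symptom scale has an intake value. The daily tracker does not, and the PPQ-II is described for postpartum people, so its intake value is doubtful for those enrolled while pregnant.
- A reader might assume that concurrent treatment is on file. The Intake Survey section lists demographics, health, mental health and pregnancy history, but does not name current treatment.
- The assumed correlations are not in the documents. The eligibility score ranges restrict the spread of intake scores and may lower ρ; the induced correlation falls in proportion (ρ = 0.3 would give 0.3 × -0.3 = -0.09).

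**Conclusion.** The point holds in conditional form. As written, the method is an unadjusted correlation at an unspecified visit. For intake scores there is nothing to correct. For midpoint, post or follow-up scores, the correlation mixes initial severity with any link between use and change. Under the assumed correlations of 0.5 to 0.7 and -0.3, the spurious part is about -0.15 to -0.21. That is below the critical value of 0.279 at n=50, but enough to raise the chance of P<.05 from 5% to roughly 18% to 31%. The distortion falls on the .05 criterion and hardly touches the 0.6 or 0.8 cutoff. The 71% figure needs much stronger assumptions and should not be quoted as the expected size.

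This is a worthwhile improvement to an exploratory secondary analysis. It does not affect the feasibility and acceptability aims. Confidence is moderate, because the plan does not say which scores it will use and the size rests on assumed correlations.

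**What to change.** Amend the Data Analysis Plan to:

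1. Name the visit for each correlation.
2. Correlate intake scores, unadjusted, with engagement and completion, and state that this addresses who engages.
3. For post-intake scores of scales measured at intake (for example EPDS, GAD-7, PHQ-9), use a partial correlation or a regression on frequency and duration of use, adjusting for the same scale at intake. Report the estimate with a 95% confidence interval, as descriptive.
4. Add pregnant or postpartum status as a covariate, and concurrent treatment only if the intake form records it.
5. Not interpret post or follow-up scores against completion rate.

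This changes wording only. The article says analysis follows the last participant's completion, and the intake scores are already scheduled. The cost is a few degrees of freedom: with three covariates, 50 - 2 - 3 = 45 instead of 48, or 33 instead of 36 at n=38. With the intake score alone, the critical value moves from 0.279 to 0.282 at n=50. In return, the residual SD falls by 13% to 29% under the assumed ρ. Confounding by care started after intake remains and should be stated as a limitation.
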